## Introduction

### Background

Diabetes disproportionately affects African-American and Latino adults in the United States compared with Whites [1]. Not only is the prevalence of type 2 diabetes approximately 1.5 times greater, but diabetes-related outcomes are consistently worse. Aggressive management of blood glucose, blood pressure, and cholesterol through medication and lifestyle adherence is necessary to minimize adverse health outcomes [2,3]. However, fewer than 20% of African-Americans and Latinos reach all therapeutic goals [4-11]. Adherence to medication is generally poor [12]: 20%-30% of prescriptions are never filled (due to cost or concerns of side effects), and 50% of medications for chronic disease are not taken as prescribed [13-15]. Additional barriers to physical activity [16] and healthy eating [17] behaviors are common within urban neighborhoods where low-income African-Americans and Latinos reside. Access to healthy foods and safe areas for physical activity are often limited. As a result, adherence to the recommended diet and physical activity is low for a majority of minorities with type 2 diabetes [18,19]. Additional barriers to self-management among low-income, minority populations include low health literacy, depression, lack of social support, poor patient-clinician communication, limited access to health care, and language (particularly Latinos who prefer Spanish for communication with providers) [20-27].

Four large systematic reviews of intervention studies aimed at improving medication adherence have concluded that few existing interventions improved clinical outcomes beyond adherence alone [13,14,28,29]. In addition, the reviews highlighted concerns regarding the abundance of studies with small sample sizes and the underrepresentation of ethnic minorities, especially Latinos. Components of the most effective interventions often included behavioral strategies and incorporated pharmacists [30]. Pharmacist-led interventions enhance adherence to chronic disease medication and health behaviors through patient education, use of adherence aids, and addressing medication-related issues (eg, drug interactions and cost) [14,31-36]. Clinical pharmacists have expertise in medication management and the ability to adjust therapy in collaboration with providers [37-42]. Within the United States, most state boards of pharmacy authorize collaborative drug therapy management protocols between clinical pharmacists and prescribers [42-45].

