More recently, 2 pragmatic studies of chronic disease management employed multifaceted interventions delivered by clinical pharmacists using telephone-based brief negotiated interviewing, a variant of motivational interviewing [46,47]. First, Choudhry et al [46] studied patients within a large multispecialty medical group including 488 patients with diabetes and others with hypertension or hyperlipidemia that were poorly controlled. A statistically significant improvement in medication adherence failed to translate into any significant improvement in clinical outcomes for patients with diabetes or the other chronic conditions. In the second study, Lauffenburger et al [47] enrolled members of the largest health insurer in New Jersey with similar results. However, in a secondary analysis of 196 participants with diabetes who completed at least one telephone pharmacy consultation, hemoglobin A_1c_ (HbA_1c_) decreased (difference between intervention and propensity score matched comparison group: mean decrease in HbA_1c_−0.48 with a 95% CI of −0.91, −0.05). Although both studies included ethnic minorities, subgroup analyses to explore the impact of the intervention based on ethnicity were not reported.

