Health coaches (HCs) may extend the ability of clinical pharmacists to support medication adherence in low-income minority populations. HCs alone have been shown to contribute to improvements in diabetes self-management and HbA_1c_ levels [48-55]. Trained HCs are trusted by patients, understand sociocultural barriers, and can help increase the relevancy of disease self-management to individuals who manage competing priorities. Our previous research demonstrated that HCs can successfully collaborate with clinical pharmacists in addressing lifestyle and medication adherence [56], with unclear evidence of improved clinical outcomes [15]. In our initial efficacy trial of African-American and Latino patients with uncontrolled type 2 diabetes, we demonstrated a modest reduction in HbA_1c_ with pharmacist support alone (mean decrease in HbA_1c_ −0.45%; with a 95% CI −0.96, 0.05), which was similar to the change observed with HC-augmented pharmacist support (mean decrease in HbA_1c_ -0.42% with a 95% CI −0.93, 0.08). However, many participants did not fully engage with the pharmacists, which required transportation to the clinic for in-person visits. Importantly, 80.4% (152/189) of our study sample surveyed expressed interest in participating in a mobile health (mHealth) approach with pharmacists and HCs.

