Intermediate variables are also collected at each of the 5 time points. Perceived severity of diabetes and perceived susceptibility are assessed using 2 items adapted from the study by Bradley et al [92]. The perceived benefits of therapy are measured by a 5-item survey related to the benefits of therapy [71]. Diabetes distress is measured using the brief Diabetes Distress Scale [73]. Depression is measured using the Patient Health Questionnaire [75,76]. Social support is measured using an assessment of the amount of total support received and satisfaction with support from family, friends, and the health care team [93]. Self-efficacy is measured using the Stanford 8-item self-efficacy for diabetes survey [94]. Contextual data include an environmental survey that addresses loneliness, social cohesion, and neighborhood safety as well as the identification of stressful life events [95-97].

HCs record the dates of patient contacts in REDCap (eg, phone calls and home encounters). Clinical progress notes are completed in the EMR after every participant contact (by phone if longer than 15 minutes and in-person). Information includes mode, time, location (home vs clinic), content of contact, results of glucose or blood pressure self-monitoring, goals, life events, pharmacist interactions, and interventions. Intensification of therapy will be defined as the number of dosage increases of antihypertensive, hypoglycemic agent, or insulin or the addition of a new agent since the baseline visit [98-100]. Chart review will define the number of PCP visits and pharmacist videoconferences as well as the number of pharmacist- or physician-initiated medication changes.

*Physiologic outcomes* will be collected at 5 time points (0, 6, 12, 18, and 24 months). The research staff will perform phlebotomy, blood pressure, weight, and height recordings. HbA_1c_ and fasting lipid profile (total cholesterol, high-density lipoprotein, LDL, and triglycerides) are obtained via phlebotomy. A calibrated digital scale measures weight. A height stadiometer measures height, with subjects removing their shoes (for BMI assessment). Blood pressure is assessed in subjects sitting down for at least 5 minutes, following a standard procedure. Health-related quality of life is measured using the EuroQol Group 5D and Diabetes Distress Scale [73].

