Exploratory subgroup analyses will follow a heterogeneity in treatment effects framework [113,114]. We will determine which subjects in the intervention group had the greatest improvement in outcomes, based on multiple prespecified patient characteristics, including race (African-American or Latino), depression, comorbidities, baseline behaviors, health literacy, continuity of care, and social support. These analyses will also consider additional comparisons between subjects above and below the median levels of videoconferencing and text messaging activity. Statistical tests will be implemented as interactions within the full data set.

If the intervention results in improved HbA_1c_ more than that in the usual care, we will examine whether changes in self-efficacy, health beliefs, or social support serve as mediators for improved outcomes. In addition, we will explore diabetes-related behaviors as well as medication treatment intensification as mediators using MPlus [115-118]. To further identify the relative contributions of videoconferencing and/or text messaging, we will conduct meditational modeling with videoconferencing time, number of text messages, and HC contact time as mediating variables. This may describe any dose-response relationship between mHealth utilization and outcomes. We will compute bias-corrected bootstrap standard errors using MPlus. This offers accurate confidence intervals for mediation coefficients [119]. Due to anticipated relationships between HC activity level and mHealth delivery, we plan to inspect correlations between mediators and incorporate any significant findings in model development. This analysis will demonstrate whether the intervention effects are sensitive to mediators. Finally, given the sample size, observed (rather than latent) variables will be used in the mediation models. To enhance the power of mediation modeling, we adopt an α=.10 type I error criterion to improve the chances of finding promising mediators for future studies.

We expect a limited amount of decline in physiologic outcomes with the transition back to usual care. We will test the hypothesis that improvements in HbA_1c_ (primary outcome), blood pressure, and LDL cholesterol (secondary outcomes) will be maintained during the maintenance period. The analyses will be conducted in a manner similar to our primary hypothesis and will evaluate changes in the initial intervention group 1 year after intervention completion.

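### Mediation by self-efficacy, health beliefs and social support is conditional on an HbA1c benefit, so after a null result the article commits to no analysis of whether these constructs moved

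*Protocol article*

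**What the plan says.** In the protocol article, Methods, Data Management and Analysis, the mediation paragraph opens with a condition: "If the intervention results in improved HbA_1c_ more than that in the usual care, we will examine whether changes in self-efficacy, health beliefs". The sentence goes on to name social support as the third candidate mediator. The next sentence adds more mediators without repeating the condition: "In addition, we will explore diabetes-related behaviors as well as medication treatment intensification as mediators using MPlus". A later one turns to delivery dose, again without it: "we will conduct meditational modeling with videoconferencing time, number of text messages, and HC contact time as mediating variables". The paragraph ends by relaxing the error rate, "we adopt an α=.10 type I error criterion", so as to raise the chance of spotting mediators that later studies could take up.

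On measurement, the Data Collection section states: "Intermediate variables are also collected at each of the 5 time points". Its list includes perceived severity, susceptibility and benefits, social support, and self-efficacy.

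Elsewhere, the Objectives section hypothesizes, with no condition, that medication and lifestyle adherence will improve against usual care. Study Design names blood pressure and LDL cholesterol as the secondary outcomes. The joint model in Data Management and Analysis covers the physiological outcomes.

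**The concern.** A significant total effect is not a prerequisite for an indirect effect. Paths of opposite sign can cancel, and the test of the total effect can have less power than the tests of the component paths. The condition therefore removes an analysis that remains valid and informative when HbA1c does not improve.

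The article's own Background shows why that case matters. It reports of existing adherence interventions that "few existing interventions improved clinical outcomes beyond adherence alone", and of one pragmatic pharmacist study that "A statistically significant improvement in medication adherence failed to translate into any significant improvement in clinical outcomes for patients with diabetes". A trial that ends this way will be asked where the chain broke. For self-efficacy, health beliefs and social support, the article as written promises no answer in that case. The condition also pulls against the relaxed alpha in the same paragraph: alpha is raised to find candidate mediators, while the condition cancels the search after a null result.

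At stake is the explanatory content of a null trial. No primary or secondary estimate is affected.

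**Working it through.** **Inputs.** From Sample Size Justification: SD 1.8, effect size 0.56 (unit not stated), cross-time correlation 0.30 with compound symmetry, ICC 0.01, 5 clusters, design effect 1.34, two-sided alpha .05, 80% power, 20% dropout, 220 patients. From Background: decreases of 0.45 and 0.42 points in the team's earlier trial, both intervals including zero, and 0.48 points in a cited secondary analysis, interval excluding zero. The article sets no significance level for the condition; two-sided p<.05 is assumed here.

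**The plan's own figures.** Completers: 220 × 0.8 = 176. Design effect: 1 + (176/5 − 1) × 0.01 = 1.342, which matches. The total of 220 does not reproduce exactly. The nearest natural form, a change score at 0.56 SD, needs 142 × 1.34 = 191 completers, and 191/0.8 = 239. That is a separate matter, and nothing below depends on it.

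**Probability that the condition is unmet.** Effective patients per arm: 176/1.34/2 = 65.7. For the year-1 parallel analyses, SE = 1.8 × √(2v/65.7), with variance factor v:
- single follow-up value: v = 1, SE = 0.314
- change score: v = 2(1 − 0.3) = 1.4, SE = 0.372
- mean of the 6- and 12-month values, baseline-adjusted: v = (1 + 0.3)/2 − 0.3² = 0.56, SE = 0.235

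For a two-period crossover without carry-over, SE = ½ × 1.8 × √(2 × 1.4/65.7) = 0.186.

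With z = effect/SE, P(unmet) = Φ(1.96 − z). At 0.45 points on the change score, z = 0.45/0.372 = 1.21 and Φ(0.75) = 77%.

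| Analysis | 0.42 to 0.48 points | 0.56 SD = 1.01 points |
|---|---|---|
| Single follow-up | 73% to 67% | 11% |
| Change score | 80% to 75% | 23% |
| Mean of two, baseline-adjusted | 57% to 47% | 1% |
| Crossover, no carry-over | 38% to 27% | 0% |

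If 0.56 is read as HbA1c points, the range across these models is 15-67%.

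**Sensitivity.** Without the design effect (88 per arm), the figures at 0.45 points fall to 71% (change score), 40% (mean of two, baseline-adjusted) and 20% (crossover). Carry-over works the other way. If a fraction m of the year-1 benefit persists into year 2, the simple crossover contrast shrinks to (1 − m/2) of the true effect. At 0.45 points, z = 2.42 with m = 0, 1.82 with m = 0.5 and 1.21 with m = 1, so the condition is unmet in about 32%, 56% and 77%. The article hypothesizes maintenance.

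**What an unconditional analysis could show.** With 65.7 effective patients per arm, a test of the intervention's effect on a mediator has 63% power at 0.4 SD and 82% at 0.5 SD (alpha .05), or 74% and 89% at the plan's alpha of .10, whatever HbA1c does. The mediator effects of 0.4 and 0.5 SD are assumptions; the article gives none.

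**The case against.** Asking what mediated an improvement only when there is one is a conventional sequence, and the work is exploratory. The condition is explicit for three constructs only; extending it to behaviors, intensification and delivery dose is an inference from paragraph order. The Background evidence concerns adherence, and the between-condition hypothesis on adherence carries no condition. All of this stands, and it limits the point to three exploratory constructs plus an ambiguity of scope. It does not justify the condition, which is a stated rule and not a detail left to a fuller document.

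Three stronger readings are tempting, and the article does not support them.

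- **That a null result is likely.** The evidence cited is mixed. The article also reports better glycemic outcomes with telemedicine, reductions of 0.4 to 1.7 points in successful education programs, and the 0.48-point secondary analysis. The team's 0.45-point decrease, "which was similar to the change observed with HC-augmented pharmacist support", is given with no stated usual-care comparison, so using it as a between-arm effect is an assumption. The article also says that many participants in that trial did not fully engage with the pharmacists, who had to be seen in clinic; home videoconferencing is meant to address this.
- **That the trial could not say whether the mechanisms moved.** The variables are collected at every visit, so the contrasts can be estimated. What is missing is a commitment to estimate them.
- **That the condition inflates the mediation estimates.** In a positive trial the same models give the same numbers with or without it. Overstatement given significance (about 1.2- to 2.2-fold at 0.42 to 0.48 points) concerns the total HbA1c effect. For the indirect effect it is about 1.05- to 1.31-fold under assumed mediator effects of 0.4 to 0.6 SD, and deleting the condition would not change it.

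**Conclusion.** The point holds in limited form and is minor. The article makes the mediation analysis of self-efficacy, health beliefs and social support depend on an HbA1c benefit, leaves the scope of that condition unclear for the other mediators, and so commits to no analysis of the three constructs after a null result. The condition is not statistically required and conflicts with the paragraph's stated purpose.

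How often it would bite depends on the model and the true effect. At about 0.45 points it is unmet in roughly half to four fifths of trials under year-1 parallel analyses with the design effect applied, and in about a third under a crossover without carry-over. At 0.56 SD it is unmet in at most about 23%. These figures rest on reading the condition as two-sided p<.05 and on treating the earlier decreases as between-arm effects, neither of which the article states.

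**What to change.** Delete the opening condition. State that, whatever the HbA1c result, the year-1 between-arm effect on each intermediate variable will be reported with its confidence interval, and that the planned mediation models will be run for all listed mediators and labelled exploratory. This also settles the scope for behaviors, treatment intensification and delivery dose.

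The cost is a change of wording and a few extra model runs on data already being collected. The downside is more exploratory estimates to report, which the label should make plain.

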**Figure 1 figure1:**
[figure not shown]
Randomized crossover study design.

The primary outcome is the change in HbA_1c_ level. Secondary outcomes include changes in blood pressure and LDL cholesterol levels. Using a 1:1 ratio, we will randomize 220 patients to either (1) a mHealth intervention delivered by a clinical pharmacist and HC for 1 year, followed by usual care for 1 year, or (2) usual care for 1 year, followed by the mHealth intervention for 1 year. Both groups will crossover at the end of year 1, such that those receiving the mHealth intervention during the first year will receive usual care during the second year (to evaluate potential maintenance of outcome improvement). Similarly, those with usual care in year 1 will crossover to receive the intervention in year 2 (to ensure that all subjects are able to receive the intervention). Of note, we do not consider HbA_1c_ levels collected at the end of year 1 when crossover occurs. The treatment received by patients (intervention or usual care) will change at the end of year 1, independent of HbA_1c_ levels.

Separate randomization schedules generated in REDCap will be used for each of the 4 main clinical sites with stratification for ethnic group (African-American and Latino) and gender to balance the proportion of participants across randomized conditions. All study procedures have been approved by the University of Illinois at Chicago Institutional Review Board (IRB 2016-0380).

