Pharmacist services are based on a standardized pharmacist management protocol. After the initial medication reconciliation, follow-up pharmacist activities include reviewing home glucose and/or blood pressure, monitoring log data obtained by the HC during home visits, identifying therapeutic goals for HbA_1c_ and blood pressure collaboratively with patients’ primary care providers (PCPs), formulating an approved plan of care, assessing changes in medications, and documenting the plan in the EMR. In addition, pharmacists provide education related to medication (name and purpose of medications and time, strength, and method of administration); drug interactions and side effects; goals of therapy; basic lifestyle modifications; and use of pillboxes, low-literacy visual medication lists, or other adherence aids. Pharmacists educate and encourage lifestyle changes, consistent with the published guidelines [67-69]. They propose medication changes based on algorithms and protocols derived from national guidelines under physician guidance [70-72]. Pharmacists routinely monitor hypoglycemic events, address prevention, and review treatments. This includes 3 steps: (1) addressing hypoglycemia with every patient contact, (2) applying principles of appropriate therapy (education, empowerment, frequent glucose self-monitoring, flexible medication regimen, individualized goals, and professional guidance), and (3) considering risk factors for hypoglycemia. Overall, there is mixed evidence regarding the benefits of aggressive glycemic control [73-75]. In the proposed study, PCPs and pharmacists adopt the American Diabetes Association approach to individualized care, where the general goal for nonpregnant adults is HbA_1c_ less than 7%. They may decide upon less stringent goals for those with a history of severe hypoglycemia, limited life expectancy, advanced complications, or extensive comorbid conditions [76]. In addition, pharmacists follow the 2018 American College of Cardiology or American Heart Association guidelines for lipid management (eg, calculating 10 year atherosclerotic cardiovascular risk to determine statin intensity) [77].

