#### Sample Size Justification

The sample size calculation is powered to detect the primary outcome, which is the change in HbA_1c_. Reviews of published studies suggest that successful education programs lower A_1c_ levels by 0.4% to 1.7% [3,103]. On the basis of our previous experience with the patient population, we estimated a mean baseline HbA_1c_ level of 10% with a SD of 1.8 and an effect size of 0.56 for aim 1. The cross-time correlation was estimated to be 0.30, with a compound symmetry structure. We adjusted for clustering and assumed an intraclass correlation coefficient of 0.01, with 5 clusters. This yielded a design effect of 1.34. Two-sided alpha of .05 and 80% power were assumed. Allowing for a 20% dropout rate, 220 patients were required [104].

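### The planned intensification count can substantially under- or over-state how much of the HbA1c effect runs through medication changes, because the count plausibly responds to HbA1c itself

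*Protocol article*

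**What the plan says.** All references are to the protocol article.

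- **Mediator.** Under Data Management and Analysis: "In addition, we will explore diabetes-related behaviors as well as medication treatment intensification as mediators using MPlus". This is done only if HbA1c improves more than under usual care, with bias-corrected bootstrap standard errors and a type I error criterion of .10. The one safeguard described is to inspect correlations between mediators.
- **Definition.** Under Data Collection: "Intensification of therapy will be defined as the number of dosage increases of antihypertensive, hypoglycemic agent, or insulin". Newly added drugs count as well, and the window is cumulative from baseline. Chart review is to supply the number of medication changes initiated by a pharmacist or physician.
- **How changes arise.** Under Clinical Pharmacist: "They propose medication changes based on algorithms and protocols derived from national guidelines under physician guidance". Pharmacists and primary care providers follow an individualised approach, "where the general goal for nonpregnant adults is HbA_1c_ less than 7" (per cent). Entry requires HbA1c of at least 8.0%, so every patient starts above that general goal.
- **Outcome and timing.** Under Study Design: "The primary outcome is the change in HbA_1c_ level". HbA1c is measured at 0, 6, 12, 18 and 24 months.

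The mediation text does not mention earlier HbA1c as a confounder, or the time order of medication changes and HbA1c values.

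**The concern.** A mediated effect is built from two paths: arm to mediator, and mediator to outcome given arm. Randomisation protects the first path but not the second.

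Under goal-directed care, patients whose HbA1c stays high will tend to receive more dose increases and new agents. Within each arm the count is then partly a consequence of HbA1c as well as a possible cause of it, which is confounding by indication. Adjusting for baseline HbA1c removes only part of the problem, because changes made after month 6 can respond to HbA1c at month 6. A count accumulated since baseline hides that sequence.

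The definition also mixes in antihypertensive increases. These are not made in response to HbA1c and are not expected to lower it, so they weaken the estimated effect per counted change.

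At stake is the mechanistic reading of a pharmacist programme. An effect that runs through medication could be credited to something else, or the reverse, and the article intends these results to pick out mediators for later studies.

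**Working it through.** The article gives no figure for the mediated effect, so there is nothing to reproduce. The check asks what simple mediation models return when the truth is known.

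**Inputs from the article.** Baseline mean and SD: "we estimated a mean baseline HbA_1c_ level of 10% with a SD of 1.8 and an effect size of 0.56 for aim 1". Only the mean of 10 and SD of 1.8 are used. The cross-time correlation is 0.30 with compound symmetry (Sample Size Justification). Visits are at 0, 6 and 12 months.

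**Assumptions not in the article.** The number of changes in each six-month interval is Poisson with

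log(rate) = log(0.6) + 0.5 × arm + g × (HbA1c at interval start - 10).

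The trigger strength g is 0 to 0.3 per HbA1c point. Over one SD this multiplies the rate by exp(0.1 × 1.8) = 1.20 to exp(0.3 × 1.8) = 1.72. Each change lowers HbA1c by 0.2, 0.35 or 0.5 points, and the direct effect of the arm is -0.2. Every simulated change is glucose-lowering. The entry cut at 8% is not modelled. There are 400,000 patients per setting, so the results show bias and not sampling noise.

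**Quantity.** Let a be the arm difference in the 12-month count, b the coefficient of the count in the outcome model, and β the true effect per change. The ratio is (a × b) / (a × β). A ratio of 1 is correct.

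**Results at correlation 0.30**

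| Effect per change | g | Month-12 HbA1c on arm and count | Same, plus baseline HbA1c | Change score on arm and count |
|---|---|---|---|---|
| -0.2 | 0 | 1.01 | 1.01 | 1.01 |
| -0.2 | 0.1 | 0.51 | 0.82 | 1.54 |
| -0.2 | 0.2 | 0.14 | 0.67 | 1.99 |
| -0.2 | 0.3 | -0.06 | 0.57 | 2.26 |
| -0.35 | 0.1 | 0.73 | 0.91 | 1.33 |
| -0.35 | 0.2 | 0.51 | 0.82 | 1.59 |
| -0.35 | 0.3 | 0.37 | 0.75 | 1.75 |
| -0.5 | 0.1 | 0.81 | 0.93 | 1.22 |
| -0.5 | 0.2 | 0.65 | 0.87 | 1.42 |
| -0.5 | 0.3 | 0.55 | 0.81 | 1.53 |

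With g = 0 all three models are right for every effect size, so the bias comes from the trigger. The change score errs upward because patients with high baseline HbA1c receive more changes and also fall by regression to the mean. The model credits that fall to the changes.

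**Sensitivity, correlation 0.60.** With a trigger, the ranges are -1.02 to 0.62 (level), 0.48 to 0.92 (baseline-adjusted) and 1.12 to 1.67 (change score).

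**Second simulation at trial size.** This used n = 220 × 0.8 = 176, 400 trials per setting, a true effect per change of -0.30, all of the effect mediated, and rates rising by exp(0.25), exp(0.5) or exp(0.75) per 1.8 points. Mean coefficients, with ratio to -0.30:

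- Level: -0.13, -0.04, -0.03 (0.43, 0.13, 0.10).
- Baseline-adjusted: -0.26, -0.22, -0.19 (0.87, 0.73, 0.63).
- Change score: -0.42, -0.48, -0.47 (1.40, 1.60, 1.57).

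The ordering and directions are the same.

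**Check of the remedy.** When the second-interval count was used with arm, baseline HbA1c, month-6 HbA1c and the earlier count as covariates, the coefficient was 0.98 to 1.02 times the truth in every setting of the large simulation. Interval counts in the second simulation gave -0.31, -0.30 and -0.30. This validates the path from count to HbA1c, not a full mediated effect.

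**Antihypertensive changes.** These were not simulated. Suppose the total is G + H, with G glucose-lowering and H antihypertensive, and suppose that within arm H is independent of G and has no effect on HbA1c. Leaving the trigger aside, the coefficient per counted change is β × Var(G) / (Var(G) + Var(H)), which is smaller than β in size. The effect on the product a × b also depends on the arm difference in H, so the claim here is limited to the per-change path.

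**The case against.** The strongest reply is that the article fixes no mediation model. It names the software and cites methods sources. It does not give the outcome form, the covariates, or whether a single 12-month total enters. Its main analysis allows for time-varying covariates, and a fuller plan may set the time order. This stands: nobody can say which column of the table the trial would land in. What remains is what the article does fix, namely a count since baseline, antihypertensives included, used as a mediator of HbA1c, with a safeguard aimed only at correlations between mediators.

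Second, the dependence of medication changes on HbA1c is inferred from the goal and the algorithms. No trigger rule is written, and its strength is unknown. This also stands, and it is why the percentages are illustrations. The inference itself is plausible for goal-directed care.

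Third, the conventional baseline-adjusted model shows only moderate attenuation. That is so: 0.57 to 0.93 at the article's correlation, and 0.48 to 0.92 at 0.60.

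Fourth, the analysis is exploratory and conditional on a positive HbA1c result. That limits the weight of the point but does not remove it.

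A reader might infer that the plan yields a mediated effect within some definite multiple of the truth, or that it is always biased towards intensification not helping. The documents support neither. Any single range pools models the article does not choose between, under assumed inputs, and the change score, a natural reading given the stated primary outcome, errs the other way.

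**Conclusion.** The concern holds in a limited form. Using the defined count as a mediator of the HbA1c effect can substantially misstate the mediated effect if medication changes respond to HbA1c.

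- Month-12 level without baseline adjustment: under-estimate, with possible sign reversal.
- Level with baseline adjustment: attenuated.
- Change score without baseline adjustment: over-estimate.

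The sizes rest on the assumed trigger strength, effect per change, base rate, arm effect on the rate and direct effect. With no trigger the bias disappears. Including antihypertensive changes further dilutes the estimated path per change, by an amount the documents do not allow to be computed. The primary HbA1c comparison does not use this count and is unaffected. The change is worth making because it is cheap, not because the trial's main conclusion is at risk.

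**What to change.** For the HbA1c mediation analysis:

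1. Count only glucose-lowering changes, separately for the intervals between HbA1c visits (months 0-6 and 6-12).
2. Relate each interval's count to HbA1c at the end of that interval, adjusting for arm, baseline HbA1c, HbA1c at interval start and the earlier count.
3. Obtain the overall mediated effect with a longitudinal mediation or g-formula method. Month-6 HbA1c is both affected by earlier changes and a cause of later ones, so the interval regression alone does not give it.
4. If chart-review changes cannot be dated, or month-6 HbA1c is too often missing, report intensification by arm descriptively and do not interpret it as a mediator.

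The cost is analysis-plan wording, some recoding of chart data already due to be collected, wider intervals for the mediated effect (by how much was not computed), and reliance on month-6 HbA1c, which the article's complete-case definition does not require. No added patients, visits or changes to care are needed.
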